## Abstract

Quantitative running gait analysis is an important tool that provides beneficial outcomes to injury risk/recovery or performance assessment. Wearable devices have allowed running gait to be evaluated in any environment (i.e., laboratory or real-world settings), yet there are a plethora of different grades of devices (i.e., research-grade, commercial, or novel multi-modal) available with little information to make informed decisions on selection. This paper outlines a protocol that will examine different grades of wearables for running gait analysis in healthy individuals. Specifically, this pilot study will: 1) examine analytical validity and reliability of wearables (research-grade, commercial, high-end multimodal) within a controlled laboratory setting; 2) examine analytical validation of different grades of wearables in a real-world setting, and 3) explore clinical validation and usability of wearables for running gait analysis (e.g., injury history (previously injured, never injured), performance level (novice, elite) and relationship to meaningful outcomes). The different grades of wearable include: (1) A research-grade device, the Ax6 consists of a configurable tri-axial accelerometer and tri-axial gyroscope with variable sampling capabilities; (2) attainable (low-grade) commercial with proprietary software, the DorsaVi ViMove2 consisting of two, non-configurable IMUs modules, with a fixed sampling rate and (3) novel multimodal high-end system, the DANU Sports System that is a pair of textile socks, that contain silicone based capacitive pressure sensors, and configurable IMU modules with variable sampling rates.

**Clinical trial registration: Trial registration**: NCT05277181.

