#### Laboratory testing

Laboratory testing will be conducted at the biomechanics laboratory Northumbria University, Newcastle upon Tyne, United Kingdom. Within the controlled laboratory environment, we will conduct a concurrent data collection with the multimodal, commercial, and research-grade wearables to determine their validation and reliability for running gait analysis compared to laboratory reference standards (3D motion capture and force plates). Recruitment for the laboratory testing began in September 2021 with an expected end date September 2023.

*Participants*. Within the laboratory testing 40 individuals will be recruited, specifically 20 with and 20 without a history of previous lower limb injury (but fully recovered at time of assessment and able to run safely, in line with inclusion / exclusion criteria).

*Laboratory reference set-up*. As previously described, a 3D motion capture and force plate system will be used as the ‘gold-standard’ reference measures.

*Running procedures*. All participants will run overground and, on a treadmill, (Spirit fitness XT485). Participants will be provided with a standardised, neutral cushioning running shoe (Saucony Guide Runner) to wear during testing in order to remove bias [34]. Prior to testing, participants will run on the treadmill at a comfortable speed for a warm-up and to familiarise themselves with running on a treadmill. Participants will be allowed breaks at any point or permitted to abort the trial at any time. For the overground segment, participants will run at a comfortable self-selected speed overground for 10m intermittently, where they will be asked to foot-strike two staggered force plates in the middle of the run (~5m point). Practice trials will be performed prior to data collection to allow participants to adjust their start position to strike the force plates correctly. A total of five successful recordings for each of the left and right leg will be captured. For the treadmill segment, participants will be asked to run at five speeds, four of these speeds will be standardised (i.e., 8, 10, 12 and 14 km/hr) and one speed will be their self-selected speed. Self-selected speed will be determined by the participant’s 5km personal best. The order of speed will be consistent across participants, starting at the slowest speed and progressing to the fastest to ensure the safety of participants. Data will be collected for 60s at each speed.

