*Initial data processing*. Data will be collected simultaneously by the measurement systems, at the commencement and conclusion of each task, the time will be synchronized with a laptop and recorded by the assessor (i.e., time-stamp extraction). At the end of each testing session, the wearable and reference device data will be download onto a computer and stored in secure servers for further data processing and analysis.

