### Sample size calculation

This is the first study (pilot study) to use the novel multi-modal wearable system (DANU system) for gait analysis in any population, alongside other wearables and gold-standard measures. As such, there are few specific previous examples were available to guide estimates for sample size. Previous research that has shown statistically significant outcomes when investigating wearables for running gait assessment in sport have had sample sizes ranging from 1 [41] to 187 [42], with the average number of participants at 26 [21]. Thus, a sample size of 40 participants for analytical validation (i.e., comparison to gold-standards) is feasible and adequately powered [43, 44].

Regarding the exploratory clinical validation analysis, a sample size of 20 participants per group for the performance and clinical group analysis is adequate in this initial exploratory pilot study. While there are no specific rules for sample size calculations in pilot / initial exploratory studies, evidence suggests that 10–12 participants per group may be adequate, and that 20–30 participants per group would be enough to provide valid evidence to draw scientific conclusions [43–46]. Further to this, evidence suggests that to capture 85–90% of use issues 15–20 people per group are required for usability studies [46], therefore our sample of 20 participants per group should be adequate for this initial analysis. Following from the present pilot study, future research can calculate more specific sample sizes and control for relevant variables based on the presented findings.

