### Statistical analysis

#### Analysis common to all studies

The statistical analysis will be performed using statistical software SPSS 25 (SPSS Inc., Chicago, Illinois, USA). Demographic characteristics will be summarised using descriptive statistics, including mean, standard deviation, median, minimum, maximum, and inter-quartile range for continuous or ordinal data and percentages for categorical data. The descriptive statistics will be tabulated and presented graphically for clarity. All data will be checked for normality distributed with Shapiro-Wilks tests before conducting parametric tests. Non-normal continuous distributions will be transformed where appropriate to meet the requirements of parametric tests; otherwise, the equivalent non-parametric tests will be adopted. Data will also be assessed graphically (such as histograms or scatter plots) for clarity of information. Statistical significance will be determined at p < 0.05 unless otherwise stated. Due to the experimental nature and novelty of the work and wearable systems, we will not control for multiple comparisons in order to avoid a Type II error.

*Analytical validation analysis*. To examine analytical (concurrent) validation of the wearable devices (research-grade, commercial, novel multimodal) for running gait measurement, we will compare outcomes to relevant reference measures (i.e., force plates for ground contact time) in all laboratory testing participants (n = 40). To compare running gait outcomes from the wearables and reference systems, the absolute difference, Pearson’s correlation (r), intraclass correlations (ICC), the level of agreement through the Bland Altman plots, and 95% Limits of agreement (LoA) will be calculated [48]. Accuracy will be evaluated in terms of root mean squared errors (RMSEs).

To determine test re-test reliability of the wearables, r, and ICCs between the two testing time-points will be calculated [49]. A predefined ICC performance scale will be used, defined as poor (<0.50), moderate (0.50–0.75), good (0.75–0.90) or excellent (>0.90) [50]. ICC is a common statistic for evaluating repeatability and is needed to calculate the minimally detectable change (MDC) [51, 52]. The standard error of measurement (SEM) and standard deviation (SD) will also be calculated. Laboratory based analytical validity and reliability outcomes will be descriptively reported and discussed across research-grade, commercial and novel multi-modal wearable devices.

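### The laboratory arm records all three wearables and the reference on the same runs, but compares the devices only in words, so chance differences between them cannot be told from real ones

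*Protocol article*

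**What the plan says.** The Abstract gives the motive: many grades of device exist "with little information to make informed decisions on selection". Under Laboratory testing the article states that "we will conduct a concurrent data collection with the multimodal, commercial, and research-grade wearables", set against motion capture and force plates. Initial data processing adds: "Data will be collected simultaneously by the measurement systems".

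Under Analytical validation analysis, each wearable is compared with its reference by absolute difference, Pearson's r, ICC, Bland-Altman plots, 95% limits of agreement and RMSE. Retest reliability uses r and ICC, with SEM and MDC. ICCs are labelled poor, moderate, good or excellent with cut-offs at 0.50, 0.75 and 0.90. The step across devices is then fixed: laboratory results "will be descriptively reported and discussed across research-grade, commercial and novel multi-modal wearable devices".

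A quantitative comparison between devices is planned for the real-world arm, as agreement statistics between wearables. That arm has no reference system.

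In the Discussion, the section on exploratory clinical validation says the study will establish which grade may be needed for meaningful real-world data. The Practical implications section says the suitability of each device can be evaluated.

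**The concern.** The plan quantifies differences between devices where no reference exists, and only narrates them where one does. Agreement between two wearables on the real-world course shows that they differ, not which one is wrong. Only the laboratory arm can show that. Because its recordings are simultaneous, each runner supplies a matched set of errors, one per device. The between-device difference in error can therefore be estimated directly, with its uncertainty.

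Without that estimate, a reader choosing a device sees columns of RMSEs and ICC labels side by side. A smaller RMSE or a better label may reflect a more accurate device or only sampling variation at n = 40, and the planned output does not separate the two. At stake is how well supported the statements about grade and suitability will be. The per-device validity results themselves are not in question.

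**Working it through.** **Inputs from the article.** Laboratory n = 40; three wearables and the reference recorded together; RMSE and ICC against the reference; ICC cut-offs 0.50, 0.75, 0.90. The sample size section says "a sample size of 40 participants for analytical validation (i.e., comparison to gold-standards) is feasible and adequately powered". It gives no effect size, SD, power or precision target, so the 40 cannot be reproduced and is taken as given.

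**Inputs assumed.** Device errors normal and unbiased with equal SD; reference free of error; correlation rho between the errors of different devices on the same runs set at 0, 0.5 and 0.8; true ICC varied. None of these is in the article.

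**Step 1: what can be compared (Table 2).**
- All three devices: ground contact time, step frequency, symmetry.
- AX6 and DANU: step time, flight time, foot-strike pattern.
- ViMove2 and DANU: tibial acceleration.
- DANU only: step length.

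Pairs of devices: 3 outcomes x 3 pairs + 4 outcomes x 1 pair = 13.

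**Step 2: RMSE spread among equally accurate devices.** For each device, RMSE = sqrt(mean of squared errors over 40 runners). The ratio is largest over smallest, in 20,000 simulated studies.

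| rho | median ratio, 3 devices | ratio over 1.1, 3 devices | ratio over 1.2, 3 devices | ratio over 1.1, 2 devices |
|---|---|---|---|---|
| 0 | 1.20 | 82% | about 49% | 55% |
| 0.5 | 1.17 | 77% | 39% | 49% |
| 0.8 | 1.11 | 58% | 14% | 32% |

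**Step 3: ICC bands for equally accurate devices.** With between-runner variance 1 and error variance v, the true ICC against an unbiased device is 1/(1 + v/2), so v = 2(1/ICC - 1). An ICC of 0.75 gives v = 0.667 and 0.90 gives v = 0.222. The chance that three devices do not all share a band, for validity:

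| true ICC | rho 0 | rho 0.5 | rho 0.8 |
|---|---|---|---|
| 0.75 (cut-off) | 55% | 45% | 29% |
| 0.825 (mid-band) | 27% | 23% | 16% |
| 0.90 (cut-off) | 51% | 44% | 29% |
| 0.95 | 3% | 3% | 2% |

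For retest ICCs from 0.75 to 0.90 the range is similar, 18% to 58%. For two devices, over all ICCs tried, it is 1% to 39% for validity and 1% to 43% for retest.

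**Step 4: width of a single ICC at n = 40.** Fisher's approximation for two measurements: z = atanh(ICC), SE = 1/sqrt(40 - 1.5) = 0.161, half-width 1.96 x 0.161 = 0.316.
- ICC 0.75: z = 0.973, limits tanh(0.657) and tanh(1.289), or 0.58 to 0.86 (moderate to good).
- ICC 0.90: z = 1.472, limits 0.82 to 0.95 (good to excellent).

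**Step 5: what pairing can resolve.** The Pitman-Morgan test (correlation of sum and difference of two devices' errors, alpha 0.05) compares error SDs on the same 40 runners.

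| true error-SD ratio | rho 0 | rho 0.5 | rho 0.8 |
|---|---|---|---|
| 1.0 (false positives) | 5% | 5% | 5% |
| 1.2 | 20% | 26% | 46% |
| 1.5 | 71% | 82% | 98% |

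At rho = 0.8 and a ratio of 1.2, an unpaired F test has 8% power against 46% for the paired test, so ignoring the pairing loses information. Power for a ratio of 2 is about 99% or more.

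**The case against.** The laboratory aim is each wearable against the reference, and the planned analysis does exactly that. The article calls itself an exploratory pilot, and n = 40 is argued only for comparison with the gold standards. No ranking rule is stated. Per-device error, limits of agreement, SEM and MDC already help a user decide whether a device is accurate enough. The Discussion's sentence about grade concerns meaningful real-world data, not laboratory accuracy. All of this stands, and it keeps the point modest.

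A reader might infer that equally accurate devices will usually be ranked apart. The figures do not support that. RMSE gaps above 20% occur in fewer than half of simulated studies. Two equal devices split ICC bands in fewer than half of runs in every setting tried. Three equal devices pass one half only when the true ICC is at or very near a cut-off and their errors are little correlated, or moderately so for retest at 0.50. *Usually* holds only for gaps of about 10% among three devices, or in the trivial sense that two estimates never coincide.

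The lower correlations are also the less plausible ones. Error in the reference is shared by every device, and treadmill gait events are identified by visual inspection, so errors are likely to be positively correlated. That favours the lower end of each range. It also makes pairing more valuable.

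A further objection is that intervals and secondary contrasts belong in an analysis plan that is not shown. That would answer a complaint about missing detail. Here the article itself states how the cross-device step will be done, and the real-world agreement analysis does not fill the gap, because it has no reference.

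**Conclusion.** The point holds as a worthwhile, inexpensive improvement. It is not an error that undermines the laboratory results. The article fixes a purely descriptive comparison across devices in the one arm where simultaneous recording against a reference would allow a quantitative one, and elsewhere promises conclusions on grade and suitability. At n = 40, three equally accurate devices show an RMSE gap above 20% in roughly 14% to 49% of studies, and split ICC bands in roughly 15% to 55% when the true ICC is 0.75 to 0.90. At a true ICC of 0.95 a split is rare (2% to 3%).

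These sizes rest on assumed normal, unbiased errors, an error-free reference and error correlations from 0 to 0.8. They show what chance can do and do not predict this study's results. A three-way comparison is possible for only three of the eight outcomes in Table 2.

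**What to change.** Add to the analytical validation analysis, for every outcome shared by two or more devices:

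- the within-runner difference between devices in absolute or squared error against the reference;
- the between-device difference in retest SEM;
- a 95% interval for each, from a bootstrap that resamples runners and keeps all of a runner's devices, conditions and sessions together.

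The outcomes are contact time, step frequency and symmetry for all three devices; step time, flight time and, if measured as an angle, foot strike for AX6 and DANU; tibial acceleration for ViMove2 and DANU. Absolute or squared error is preferable to a Pitman-Morgan comparison as the main estimate, because Pitman-Morgan compares error variance only and ignores bias, which RMSE includes. Label the estimates exploratory, and limit any statement that one grade is more accurate than another to what the intervals support.

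No new data or participants are needed, but there is a cost. The 13 device pairs become up to 13 x 6 = 78 contrasts over the overground run and five treadmill speeds, before retest SEM is added. The article says "we will not control for multiple comparisons in order to avoid a Type II error", so if all devices were equal about 78 x 0.05 = 3.9 intervals would exclude no difference by chance. Power is also low, about 20% to 46%, for error-SD ratios near 1.2, so modest true differences will often stay unresolved. Both limits should be stated with the results.

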### Analytical validation aims

***Laboratory validation***: Determine the concurrent validity and test re-test reliability of wearables (research-grade, commercial and novel multimodal devices) for running gait analysis against gold-standard reference measures in adult runners.***Real-world validation***: Investigate concurrent validity of real-world running gait as measured by different wearables (research-grade, commercial and novel multimodal devices) in adult runners.

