#### Real-World environment testing

Data from the novel multimodal, commercial, and research-grade wearables will be collected within real-world environments to test the clinical / performance validity of the wearables (i.e., can they differentiate or provide meaningful data on relevant populations). Recruitment for the real-world environment testing began in June 2023 with an expected end date October 2023.

*Participants*. Within the real-world environment testing 40 individuals, specifically novice/amateur (n = 20) and expert/sub-elite (n = 20) running performance level. Performance level will be based on their 5km running time (i.e., age graded performance % [35]).

*Wearable location*. Each participant will be equipped with the DANU Sports System (socks on both feet), two Axivity AX6 sensors attached to the shoelaces and two DorsaVi ViMove2 sensors on the tibia.

*Running procedures*. All participants, regardless of performance level, will be asked to complete a 5km run on a standardised route in North-East England. The course will be run on a mixture of trail paths and concrete paths, with 174ft elevation gain throughout. Information about conditions (e.g., environment and shoes) and objective load data (e.g., time and pace) will be collected. Participants will wear their own running shoes.

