** *Spatiotemporal* **					
Ground Contact Time	The time between initial foot contact and toe-off for the same foot	**✓**	**✓**	**✓**	Force plate (overground) and 3D Motion Capture (treadmill)
Step Frequency	The number of steps taken during a given time	**✓**	**✓**	**✓**	3D Motion capture
Step Length	The distance between successive points of initial contact of the opposite foot	X	X	**✓**	3D Motion capture
Step Time	The time between two consecutive heel strikes of the opposite foot	**✓**	X	**✓**	Force plate (overground) and 3D Motion Capture (treadmill)
Foot-Strike Pattern	The way or angle when the foot first contacts the ground	**✓**	X	**✓**	3D Motion capture
Flight Time	The time between toe-off from one foot to initial contact of the other foot	**✓**	X	**✓**	Force plate (overground) and 3D Motion Capture (treadmill)
Symmetry	Any measure of imbalance between the right and left leg	**✓**	**✓**	**✓**	3D Motion capture

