To examine the analytical (concurrent) validation of running gait outcomes measured in real-world settings from the various grades of wearables in all real-world testing participants (n = 40), we will compare outcomes across the wearable devices (research, commercial and novel multi-modal) through widely used measures of agreement. The absolute difference, r, ICC, the level of agreement through the Bland Altman plots, 95% LoA, RMSEs will be calculated to evaluate agreement between outcomes generated by each wearable [48].

*Exploratory clinical validation analysis*. To provide an initial exploration of clinical (performance) validation, we will investigate group difference and relationships with clinically (or performance) relevant measures. For group differences (e.g., previous injury history or performance level), analysis of co-variance (ANCOVA), will be conducted to assess for differences between groups (injured vs non-injured, or elite vs novice) in the individual running gait outcomes (e.g., ground contact time etc.) from the novel multimodal, commercial and research-grade wearable devices during the running tasks, while controlling for demographics that are significantly related to the running gait outcomes. Relationships between running gait outcomes and demographic variables (e.g., sex, age, height, weight etc.) within groups (injured vs non-injured, or elite vs novice) will be completed through Pearson correlations within each grade of wearable device (research, commercial, multimodal).

To examine the usability of the wearable devices the SUS scores for each wearable will be calculated and visualised. To investigate differences in participant perception of the usability for each grade of wearable, separate analysis of variance (ANOVA) tests will be performed. The ANOVAs will determine the differences between the SUS scores within the different device grades between participant groups (e.g., injury history, performance level). The relationships between the SUS scores, demographics (e.g., sex, age, age-grade performance), and wearables characteristics (e.g., price, weight, and battery life) will be explored using Pearson correlations [39]. The strength of the correlation will be assessed based on Cohen’s criteria: correlations < 0.30 are considered small, correlations between 0.30 and 0.50 will be considered medium, and correlations > 0.50 are considered strong [53].

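### The real-world arm can show agreement between wearables but not concurrent validity, and step length has no second device to be compared with

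*Protocol article*

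**What the plan says.** The article has two analytical validation aims. The laboratory aim is concurrent validity and test-retest reliability "for running gait analysis against gold-standard reference measures in adult runners". The real-world aim is to "Investigate concurrent validity of real-world running gait as measured by different wearables (research-grade, commercial and novel multimodal devices) in adult runners", and it names no reference. The Abstract also lists the real-world work as analytical validation.

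Under Real-World environment testing, the equipment is the three wearables: "Each participant will be equipped with the DANU Sports System (socks on both feet), two Axivity AX6 sensors attached to the shoelaces and two DorsaVi" units worn at the shin. Participants "will be asked to complete a 5km run on a standardised route in North-East England". Conditions, time and pace are recorded, but none is assigned as a reference for a gait outcome. The same section gives the data another purpose: "to test the clinical / performance validity of the wearables (i.e., can they differentiate or provide meaningful data on relevant populations").

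The Statistical analysis section labels the real-world comparison analytical (concurrent) validation and then states that "we will compare outcomes across the wearable devices (research, commercial and novel multi-modal) through widely used measures of agreement". It lists the same statistics as for the laboratory: absolute difference, r, ICC, Bland-Altman plots, limits of agreement and RMSE. It designates none of the three devices as comparator and makes no exception for any outcome.

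Table 2 defines step length as "The distance between successive points of initial contact of the opposite foot" and ticks it for the DANU system only.

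**The concern.** Concurrent validity needs a criterion against which the device is judged. In the laboratory arm this is motion capture or the force plates. In the real-world arm all three devices are themselves on trial. Agreement between two of them does not show that either is right, and disagreement does not show which is wrong.

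The label has consequences further on. The Introduction says usefulness should be judged only once the data are known to be valid and reliable. The Discussion (Exploratory clinical validation) builds on outcomes taken to be analytically valid and expects the study to establish which grade of wearable is needed for real-world running. If agreement figures are reported as validity, that reasoning rests on evidence the real-world arm does not produce.

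**Working it through.** **Step 1: the article's own use of the term.** The Sample size calculation section glosses analytical validation as comparison with gold standards. The Discussion (Analytical validation) also describes validity as examined against gold-standard reference measures. The laboratory analysis fits this usage. The real-world analysis carries the same label without a reference.

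**Step 2: what can be compared.** Counting ticks in Table 2 gives AX6 6, DorsaVi 4 and DANU 8. With m devices measuring an outcome, the number of pairs is m(m − 1)/2.

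| Outcome | Devices | Pairs |
|---|---|---|
| Ground contact time | 3 | 3 |
| Step frequency | 3 | 3 |
| Symmetry | 3 | 3 |
| Step time | 2 (AX6, DANU) | 1 |
| Foot-strike pattern | 2 (AX6, DANU) | 1 |
| Flight time | 2 (AX6, DANU) | 1 |
| Tibial acceleration | 2 (DorsaVi, DANU) | 1 |
| Step length | 1 (DANU) | 0 |

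The total is 3 × 3 + 4 × 1 + 0 = 13 pairs, out of 8 × 3 = 24 if every device measured every outcome. Seven of 8 outcomes have at least one pair, and only 3 of 8 can be compared across all three grades.

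**Step 3: what the statistics mean without a reference.** Write device readings as X = T + B + e₁ and Y = T + B + e₂, where T is the true value and B is any error common to both. Then X − Y = e₁ − e₂. B drops out of the absolute difference, the Bland-Altman plot, the limits of agreement and the RMSE. The laboratory analysis uses RMSE as its measure of accuracy. Outdoors the same formula measures disagreement only.

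**Step 4: illustration.** The documents give no error figures, so these inputs are assumptions: 40 runners, between-runner SD of the true value 20 ms, independent noise SD 5 ms per device, and a constant bias common to both devices of 0, 20 or 40 ms. ICC(2,1) and RMSE are averages over 2,000 simulated studies.

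| Shared bias | ICC, device vs device | ICC, device vs truth | RMSE, device vs device | RMSE, device vs truth |
|---|---|---|---|---|
| 0 ms | 0.94 | 0.97 | 7.0 ms | 5.0 ms |
| 20 ms | 0.94 | 0.64 | 7.0 ms | 20.6 ms |
| 40 ms | 0.94 | 0.32 | 7.0 ms | 40.3 ms |

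These agree with direct arithmetic. Between devices, ICC = 20²/(20² + 5²) = 400/425 = 0.94 and RMSE ≈ √(5² + 5²) = 7.1 ms, whatever the bias. Against truth, RMSE ≈ √(20² + 5²) = 20.6 ms and √(40² + 5²) = 40.3 ms. An ICC of 0.94 is in the excellent band of the scale the article sets for reliability, whether the devices are accurate or 40 ms out. The first row shows that the between-device RMSE can also overstate the error of a single device.

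**The case against.** The strongest reply is that the real-world aim, unlike the laboratory aim, never promises a gold standard. The analysis section also says openly that its statistics evaluate agreement between the wearables. That agreement can be computed for 7 of 8 outcomes. The laboratory arm tests the same devices against references in 40 runners, so they will not remain unvalidated. The article also calls the AX6 a valid technology for free-living use and its algorithm previously validated. The study is an exploratory pilot, and no decision rule or sample size depends on this analysis. A list of pairs per outcome is detail that an article may leave to the full plan, and comparison across devices could be read as covering shared outcomes only.

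Much of this stands. A reader might infer that the real-world aim as a whole cannot be met. The documents do not support that: the agreement analysis is feasible for 7 outcomes, and only step length has no comparison at all. Nor do the documents say how large any shared error is. The figures in the illustration show the principle, not the size of a defect in these devices.

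What does not stand is the label. Under the article's own usage, analytical validation means comparison with a gold standard, and a full plan cannot analyse a reference that the runners do not carry. The laboratory results help interpretation but do not transfer automatically. They come from a separate 40 runners in a standardised shoe, on a treadmill or over 10 m. The outdoor runners wear their own shoes for 5 km over trail and concrete. AX6 placement is also worded differently: taped over the talus in the Equipment section, on the shoelaces outdoors.

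If the comparison is read as covering shared outcomes only, the conclusion for step length is the same: this primary outcome has no real-world comparison.

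**Conclusion.** The point holds in this form. The real-world analysis is mislabelled. For 7 of 8 primary outcomes (3 with three device pairs, 4 with a single pair) it can show inter-device agreement but neither validity nor accuracy. For step length it cannot be run. The section describing the real-world data collection gives a purpose (clinical or performance validity) that differs from the one in the aims and the analysis. This rests on Table 2, the equipment list and the stated comparison, not on any assumed error size. No sample size figure changes.

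**What to change.** 1. In the Abstract, the Analytical validation aims and the Statistical analysis section, rename the real-world aim and analysis inter-device agreement, and state that no validity or accuracy conclusion will be drawn from it. Report RMSE there as a measure of disagreement.
2. State that outdoor differences will be interpreted beside each device's laboratory error for the same outcome, noting the differences in runners, footwear and surface.
3. Limit the analysis to the 13 device pairs available in Table 2 and exclude step length from it.
4. Reconcile the purpose given under Real-World environment testing with the aims and the analysis.
5. Optionally, if the route length is actually measured and the DANU system captures every step, compare its summed step lengths with the route length. This checks mean bias over the run only, because errors in single steps can cancel. The article does not say how the 5 km was measured.

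Items 1 to 4 cost rewording and need no new data. The price is a weaker real-world claim.
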